### Statistical power

The limited number of prior micro-interventions and insufficient detail for key parameters complicates efforts to confidently generate all required parameter estimates for power calculations. Accordingly, we adopted a Monte Carlo simulation approach that tested power across a range of combinations of key statistical parameters for multilevel modelling: within-person sample size (varying from 3 to 5 estimates per person), intraclass correlation (ICC) for outcome (ranging from .3 to .6 in recognition that ICC values tend to be large for repeated measures designs), random slope variance (choosing .01, .09, and .25 to reflect small, moderate, and large amounts of variance [54]), and effect size (setting at *r* = .2 to reflect small yet practically meaningful effect size [55]).

Using the SIMR (simulation-based power calculations for mixed models) package in R [56], we tested power across these different combinations of parameter estimates, with power set at .80, alpha = .05 (two-tailed), equal allocation to intervention and control arms, and conservatively allowing for 25% attrition on an initial sample of 2800 participants at the final timepoint. We note too that Hypotheses 1 and 4 are limited to the intervention arm, and thus the sample size used for those calculations was 1050 (1400 participants with 25% attrition). Using these inputs, our simulations indicated power was > .99 for all cross-level interaction effects regardless of input values, and > .80 for all within-person effects with the exception of scenarios where: (1) the random slope variance was small, or (2) a small-to-moderate random slope variance was accompanied by a small number of within-person estimates (average cluster size of 3–4). These scenarios of small random variance coupled with a small estimated effect size are unlikely based on best available evidence from past studies [23–25]. Thus, our sample size is likely to be sufficient across a range of plausible data scenarios.

### Data analyses

At trial completion, Toluna and Talk2U will deliver password protected datafiles to the corresponding author who will clean, screen and separate state- and trait-based data for blinding purposes. Data will then be delivered to the data analysts. Analyses will be conducted in Stata. A series of linear mixed effects models will test hypotheses. H1 analyses will be limited to intervention arm participants as there is no comparable pre- and post-technique data for the assessment-only arm, while analyses for H2, H3 and H4 will include participants from both study arms.

To test H1, the immediate effects of intervention content on state-based outcomes will be explored by regressing state-based outcome measures (body satisfaction and affect) onto a time variable (0 = pre-content, 1 = post-content). For H2-H4, scores on trait-level outcome variables will be regressed onto a dummy coded time variable, with baseline as the reference category compared against post-intervention, one-week, and one-month follow-up timepoints, using random effects to allow for individual differences in amount of change in symptoms over time. Group (control = 0, intervention = 1) will be included as a cross-level moderator to test group differences in change over time (H2). The moderating effect of baseline variables on this group effect will be conducted to test H3. In evaluating H4, adherence and engagement measures will be tested as moderators of change in trait-based outcome measures over time (relative to baseline) for intervention participants. Relations among random effects of Level 1 time variables will be modelled with an unstructured covariance matrix.

Baseline differences between intervention and control participants in terms of demographic factors will be tested. Any variables shown to differ across groups will be included as covariates in analyses. Linear mixed model results will be presented in adjusted and unadjusted forms to demonstrate impact of these covariates on results.

Analyses will be conducted on an intention-to-treat basis, with participant data included based on group assignment at baseline. As the post-technique state-based measure is an indicator of use of the intervention resources, only instances where participants provide data for both pre- and post-technique will be included in analyses for H1. Missing data for group comparisons (H2) and baseline moderation effects (H3) will be handled using multiple imputation by chained equations with 50 imputations. Pattern mixture modelling using the mimix package [57] will be applied to determine sensitivity of results to non-ignorable missingness.

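### H2 compares raw change from T1 without using T1 as a covariate, which gives away precision; in same-scale H3 models the T1 outcome is its own predictor

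*Protocol article*

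**What the plan says.** Under Data analyses, the trait scores are regressed on time dummies "with baseline as the reference category compared against post-intervention, one-week, and one-month follow-up timepoints". T1 is therefore a row of the outcome, not a covariate. H2 follows from this: "Group (control = 0, intervention = 1) will be included as a cross-level moderator to test group differences in change over time (H2". H3 builds on the same model: "The moderating effect of baseline variables on this group effect will be conducted to test H3". The hypotheses (The current trial design) name gender and the T1 levels of body esteem, affect and body image self-efficacy as moderators. The last three are also the trait outcomes.

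The only covariate rule concerns demographic variables found to differ between arms; the T1 outcome score is not named. Participants are randomised after completing T1 (Participant recruitment and procedure). Missing data for H2 and H3 are filled by chained-equation imputation. Random effects of the time variables are to have an unstructured covariance.

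The Statistical power section gives no correlation between T1 and follow-up. The nearest figure is the "intraclass correlation (ICC) for outcome (ranging from .3 to .6".

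**The concern.** Because randomisation follows T1, the arms have the same expected T1 mean. Any observed T1 difference is chance, and a model that leaves it free and subtracts it in full carries that noise into every H2 contrast. Using T1 as a covariate, or fixing a common T1 mean, removes only the part that predicts follow-up. At stake is the width of the confidence intervals on the primary trait outcome and the sensitivity of the moderation tests, which need more precision than the main contrast.

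H3 has a second difficulty. When T1 body esteem moderates the effect on body esteem, the T1 row of the outcome is identical to a predictor. It has no residual variation, yet the model has to give it a covariance structure together with T2 to T4.

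**Working it through.** **Inputs.** From Statistical power: "with power set at .80, alpha = .05 (two-tailed), equal allocation to intervention and control arms"; "conservatively allowing for 25% attrition on an initial sample of 2800 participants at the final timepoint", so 2800 × 0.75 / 2 = 1050 per arm; effect size "setting at *r* = .2 to reflect small yet practically meaningful effect size"; slope variance .01, .09 or .25. Assumptions: the ICC range serves as the T1-to-follow-up correlation rho; T1 variance is 1; slope variance s adds to the follow-up variance and is uncorrelated with the intercept.

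**The plan's own figure.** r = .2 converts to d = 2(.2)/√(1 − .04) = 0.408. With 1050 per arm and change-score variance 2(1 − rho) + s, analytic power for one contrast exceeds .999 in every cell. The stated power above .99 for cross-level interactions is thus reproduced. The plan's own simulation was not rerun.

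**H2 contrast.** In a simulated complete dataset, a time-by-group mixed model and the raw difference in mean change gave the same number (0.26145).

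**Variance per participant.**
- Change score: 2(1 − rho) + s
- T1 as covariate, or common T1 mean: 1 + s − rho²
- Proportion avoidable: (1 − rho)² / [2(1 − rho) + s], which is (1 − rho)/2 when s = 0

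| rho | s | change | adjusted | avoidable variance | SE excess |
|---|---|---|---|---|---|
| .3 | 0 | 1.40 | 0.91 | 35% | 24% |
| .6 | 0 | 0.80 | 0.64 | 20% | 12% |
| .3 | .01 | 1.41 | 0.92 | 34.8% | 24% |
| .3 | .25 | 1.65 | 1.16 | 30% | 19% |
| .6 | .25 | 1.05 | 0.89 | 15.2% | 9% |

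Simulation (1050 per arm, four time points, 1500 replicates) gave losses of 33% (.3, 0), 21% (.6, 0), 31% (.3, .25) and 15% (.6, .25). Both estimators were unbiased.

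**Detectable effect, 80% power, s = 0.** 2.80 × √(2/1050) × √variance:
- rho .3: 0.145 SD as planned, 0.117 SD adjusted
- rho .6: 0.109 SD as planned, 0.098 SD adjusted

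For moderation by gender, assuming an even split, the standard error doubles. The detectable girl–boy difference is then 0.29 against 0.23 SD (rho .3) or 0.22 against 0.20 SD (rho .6).

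**Power over rho .3 to .6 and s from 0 to .25.**
- d = 0.408: above .999 either way
- 0.2 SD: .946 to .999 as planned, .989 to .9999 adjusted
- 0.1 SD (illustrative; the plan does not target it): .43 to .73 as planned, .57 to .82 adjusted

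**H3, same-scale moderator (rho .5, 1050 per arm).** The T1 residual variance given the moderator is zero to machine precision. The three-way coefficient equals the group-by-baseline interaction from an analysis of covariance at follow-up (difference below 1e-14), so it is not biased. With a random intercept only, the mean standard error was .0409 against a correct .0378, and type I error was .033 instead of .05.

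**The case against.** The strongest reply is that a time-by-group mixed model is valid, that H2 is worded as greater improvement and this contrast estimates it directly, and that no planned conclusion is shown to change. All of that stands. A reader might infer that H2 is biased or the trial underpowered. Neither follows: the estimator is unbiased, and power at r = .2 is above .999 before and after the change. Even at the lower end of the effects that the Background cites for online programmes (d = .24), power exceeds the .946 found as a minimum at 0.2 SD.

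Second, the article does not write out a group main effect, and its exact model terms could be settled elsewhere. This also stands: the free T1 difference is the usual reading, not a quoted statement.

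Third, the loss depends on a correlation the plan does not give. Body esteem remeasured within a month may correlate above .6. With s = 0 the avoidable variance is then 15% at .7, 10% at .8 and 5% at .9. The loss shrinks but does not vanish.

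Fourth, a reader might infer that the same-scale H3 standard errors are wrong by a known amount, about 6% to 13% too large. That figure belongs to a random-intercept fit, which is not what the plan describes. With an unstructured marginal covariance, simulated mean standard errors were .0416, .0378 and .0349 at rho .3, .5 and .6, against empirical SDs of .0412, .0362 and .0352; type I error was .045, .042 and .054. One fit with random intercept and time effects (n = 300) converged, with a standard error of .0932 against .0960 for the analysis of covariance. Distortion under the planned structure is therefore not shown. The degenerate T1 row remains.

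**Conclusion.** The point holds as a matter of efficiency, not validity. On the usual reading of the model, and if rho lies between .3 and .6, 20% to 35% of each H2 contrast's variance is avoidable with no slope variance, and about 15% to 35% over the plan's slope-variance grid. These are variance figures: the standard error is about 9% to 24% larger, equivalent to needing 18% to 54% more participants for equal power. The benefit lies in narrower intervals, effects well below the planning value, and the moderation tests.

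For H3, the degeneracy is exact but confined to models in which the moderator is the T1 value of the same outcome. Gender and cross-scale moderators are untouched by it. The coefficient is unbiased, and the size of any standard-error distortion depends on the random-effects structure actually fitted. This is a free improvement, not an error that invalidates the plan.

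**What to change.** For H2, model T2 to T4 only, with the T1 score as covariate (T1-by-visit allowed), group, visit and group-by-visit. Alternatively, keep T1 in the outcome vector and constrain the arms to a common T1 mean. State which of the two applies.

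For H3, test group-by-baseline (by visit) in the T2 to T4 model, so that T1 is never both outcome and predictor. The common-mean version does not cure the same-scale degeneracy, so T1 should leave the outcome vector there.

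The cost is wording only. Everyone completes T1 before randomisation, so no data are lost, and the sample size and assessment schedule stay as they are. The change should be fixed before the allocation is unblinded.

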**Fig. 2 Fig2:**
[figure not shown]
Schedule of enrolment, interventions, and assessments according to the SPIRIT guidelines

Assessment of primary and secondary trait outcomes will be conducted at baseline (T1), post-intervention (i.e., 3 days; T2), one-week (T3) and one-month follow-up (T4). Participants in the intervention condition will also be assessed on state-based body satisfaction and affect immediately after engaging with each technique. To our knowledge, this is the first chatbot to target body image among Brazilian adolescents. Therefore, a secondary aim is to assess users’ engagement and adherence. Hypotheses were formulated for overall chatbot efficacy (H1-H2), moderation effects within sub-samples (H3), and intervention engagement and adherence (H4):
**H1:** The chatbot was designed to provide immediate benefits to users. Therefore, it is anticipated that adolescents will experience improvements in state-based body satisfaction and affect at the time of engagement with the chatbot.**H2**: Adolescents randomised into the intervention condition will experience greater improvements in trait-based body esteem, affect and body image self-efficacy at post-intervention, one-week and one-month follow-up, relative to the assessment only control condition.**H3:** Based on previous research into the moderating effects of gender [30] and trait psychopathology [31, 32] on body image intervention effectiveness, it was hypothesized that intervention effects will be moderated by gender, and baseline levels of body esteem, affect and body image self-efficacy. Specifically, intervention effects will be greatest among: girls; girls and boys with lower levels of trait body esteem; girls and boys with higher levels of trait negative affect and body image self-efficacy.**H4**: With regards to user engagement and adherence, given the novelty of this intervention, analyses will be of an exploratory nature. It is, however, anticipated that greater engagement and adherence with the chatbot intervention will lead to greater improvements in trait-based outcomes.

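### On its ordinary reading, the H2–H4 mixed model has 11 variance parameters for 10 covariance elements, so random-change variances cannot be separated from residual variance

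*Protocol article*

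**What the plan says.** The section on the current trial design places the trait assessments at "baseline (T1), post-intervention (i.e., 3 days; T2), one-week (T3) and one-month follow-up (T4"), which gives one score per participant per visit.

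Under Data analyses, "A series of linear mixed effects models will test hypotheses", and "Analyses will be conducted in Stata". For H2–H4 the time variable is dummy coded "with baseline as the reference category compared against post-intervention, one-week, and one-month follow-up timepoints". Participants may differ in their course, and the model is to handle this by "using random effects to allow for individual differences in amount of change in symptoms over time". The covariance is then fixed: "Relations among random effects of Level 1 time variables will be modelled with an unstructured covariance matrix".

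The random intercept is not written out. The Statistical power section implies one, because it simulates an "intraclass correlation (ICC) for outcome (ranging from .3 to .6"), and an intraclass correlation presupposes variance between persons. No constraint on the residual variance is stated, and no fallback structure is named.

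**The concern.** A random effect for every time dummy plus a random intercept gives each participant as many random effects as visits. An unstructured covariance among them already fills the whole 4 × 4 covariance matrix of the scores. The residual variance of the mixed model then has nothing left to describe.

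This is the model for the primary trait outcome and for the secondary trait outcomes. If a flat likelihood stops the software from converging or from reporting standard errors, someone has to pick a simpler covariance once the data are in hand. That choice can change the standard errors of the primary comparison. In addition, the individual differences in change that the random effects are meant to capture cannot be told apart from measurement noise.

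**Working it through.** **The plan's own figures.** The article gives no count of variance parameters to reproduce. The nearby sample-size figure does reproduce: 1400 × (1 − 0.25) = 1050 per arm, or 2800 × 0.75 = 2100 in total. The check in step 2 uses 2100.

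**Step 1: count.** Inputs: four visits, three time dummies, an unstructured random-effects covariance (all from the article), and a random intercept (implied by the ICC).
- Distinct elements of a 4 × 4 covariance: 4 × 5 / 2 = 10.
- Random intercept plus three dummies, unstructured: 4 × 5 / 2 = 10 parameters.
- Residual variance: 1. Total 11.
- The Jacobian of the 10 covariance elements with respect to the 11 parameters has rank 10, so one parameter is free.

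**Step 2: what is free and what is not.** The marginal covariance is V = ZGZ′ + σ²I, with Z the invertible 4 × 4 design (intercept and three dummies). For any σ² below the smallest eigenvalue of V, G = Z⁻¹(V − σ²I)Z⁻ᵀ returns exactly the same V. The following results are from simulated data (n = 2100, smallest eigenvalue 0.329):

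| σ² | intercept variance | T2 change variance | log-likelihood | SE, group × T4 |
|---|---|---|---|---|
| 0 | 0.990 | 0.762 | −10040.440897 | 0.04255 |
| 0.05 | 0.940 | 0.662 | −10040.440897 | 0.04255 |
| 0.15 | 0.840 | 0.462 | −10040.440897 | 0.04255 |
| 0.25 | 0.740 | 0.262 | −10040.440897 | 0.04255 |
| 0.313 | 0.677 | 0.136 | −10040.440897 | 0.04255 |

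The T2 column is 0.762 − 2σ² (for example 0.762 − 2 × 0.313 = 0.136). The total variance of change is determined, but its division into true change and noise is not. The treatment contrast and its standard error do not move. Missing visits, imputation and covariates add nothing that separates the two parts.

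**Step 3: the readings that are identified.** Leaving the intercept out gives 6 + 1 = 7 parameters (rank 7). Making it independent of the three slopes gives 1 + 6 + 1 = 8 (rank 8). Both impose constraints:
- No intercept: baseline is uncorrelated with every follow-up.
- Independent intercept: baseline has the same covariance with every follow-up, and no follow-up variance can be below the baseline variance.

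To size the effect, assume equal variances of 1, baseline correlations of .7, .6 and .4 with T2, T3 and T4, and follow-up correlations of .7 (T2–T3), .5 (T2–T4) and .5 (T3–T4). None of these is in the article. The true change variance is 2 − 2ρ = 0.6, 0.8, 1.2. Each constrained model is fitted to this covariance S by minimising log|V| + tr(V⁻¹S). The true size of a nominal 5% test is then 2[1 − Φ(1.96 √(v_model / v_true))].

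| Reading | v_model at T2, T3, T4 | True size |
|---|---|---|
| No intercept | 1.789, 1.789, 1.663 | 0.07%, 0.3%, 2.1% |
| Independent intercept | 0.657, 0.751, 1.016 | 4.0%, 5.8%, 7.1% |

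For example, with no intercept at T2: √(1.789 / 0.6) = 1.73, so the standard error is about 73% too large.

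**Step 4: exposure.** Table 3 lists three body-esteem subscales, two affect subscales and one self-efficacy score. If each is modelled separately, H2 alone needs 6 × 50 = 300 fits.

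**The case against.** The strongest reply is that H2 tests fixed effects, and these survive. That stands: step 2 shows an unchanged standard error, and the over-full model reproduces the same marginal covariance as an unstructured residual model. A reader might infer that the planned primary test is biased or has the wrong error rate. On the ordinary reading the document does not support that. The test sizes in step 3 belong to the two constrained readings under assumed correlations.

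A reader might also infer that the model cannot be fitted at all. This is not shown. A flat likelihood can still converge: two small simulated fits (n = 300, in software other than Stata) did so without warnings, with standard errors matching those of direct change-score comparisons. Nor is it right that individual change is wholly inestimable, since its total variance is identified.

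One could further read the unstructured matrix as covering only the time effects, with an independent intercept. The wording allows this and the model is then identified, but it carries the constraints in step 3. A random-intercept-only fallback is nowhere stated, so error rates computed for one would not describe this plan.

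Finally, this is a condensed article, convergence rules commonly sit in an analysis plan that is not shown, and trait-outcome analysts are to be blinded to condition. Blinding lessens the worry about a late choice of model. But the article does state a structure, so this is not missing detail.

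**Conclusion.** The point holds in a limited form. With a random intercept in the unstructured block, the H2–H4 model has 11 variance parameters against 10 covariance elements. The random-change variances therefore cannot be separated from residual variance, whatever the sample size. This rests on the random intercept, which the ICC implies but the text does not state.

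Group-by-time estimates and standard errors are sound if the fits converge. The practical risk is failed fits or missing standard errors over many imputations and outcomes, followed by an unplanned simplification. The identified readings do not rescue the sentence, because they can give wrong standard errors: true sizes ran from 0.07% to 7.1% for a nominal 5% under the assumed correlations, and other correlations would give other sizes. The problem does not extend to H1, which uses a separate pre/post model of the state measures.

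**What to change.** Replace the random-effects wording for H2–H4 with a mixed model for repeated measures: fixed effects of time, group and group-by-time, no random effects, and an unstructured residual covariance across the four visits, estimated by REML. The moderator terms for H3 and H4 are added as fixed effects.

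This structure has exactly 10 covariance parameters and is identified. It keeps the unrestricted covariance that the authors appear to want, can be fitted in Stata, and gives the same group-by-time contrasts. A random-intercept-only model should not be offered as the alternative, because it forces equal correlations between all visits.

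The cost is one sentence. A random-slope variance is no longer reported, but on the ordinary reading it had no unique value to report.

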### Ethical issues, approval and trial registration

The research will be conducted in accordance with the ethical standards and guidelines for conducting research with young people in Brazil. Study participation is voluntary. Prior to consent and assent, parents and participants will be provided with an information sheet outlining the research procedures and associated risks. Consent withdrawal is possible at any time without cause for justification. At study completion participants will be provided with a debrief form disclosing research aims and ancillary mental health sources.

The associated ethics committees will be informed of any severe adverse events or other unintended effects of the trial intervention. This study received ethics approval from the Instituto Federal de Educação, Ciência e Tecnologia do Sudeste de Minas Gerais (4.232.804), Comissão Nacional de Ética em Pesquisa (4.582.466), and the University of the West of England (HAS 19.12.090). The study is registered with Clinical Trials. Gov (NCT04825184; website: https://clinicaltrials.gov/show/NCT04825184).

